### Randomization and blinding

In cluster randomized controlled trials it is particularly important to minimize imbalance for factors known to be highly correlated with disease outcome, in this case house construction/presence of open eaves and LLIN usage. Since all households will be provided with LLINs and the majority of homes have open eaves (89 % during baseline surveys), clusters will be stratified into two groups based solely on malaria prevalence; clusters in each stratum will then be randomly assigned to the two study arms. Stratified randomization of villages will reduce the likelihood of chance imbalances between study arms but as only a relatively small number of units can be randomized in such a cluster design, both groups cannot be assumed comparable for all factors. Baseline data on malaria prevalence and haemoglobin concentration collected from all enrolled cohort participants will be used to assess disparity in disease burden at the village level prior to study monitoring.

Observer bias will be reduced where feasible; because of the visible and obvious nature of the intervention, it is not possible to conduct ITWL installation in a blinded manner. Mosquito collector bias will be reduced by using standard CDC miniature light traps and Furvela tent traps, which do not rely on the technical ability of the fieldworker to collect specimens. Trap catches will be examined by a different person to the trap collector and they will be blinded to the trap location and intervention status. The intervention implementation, for both ITWL installation and LLIN distribution, will be monitored closely for quality and to document any bias between the clusters. Epidemiological data entry will be conducted using smartphones to minimize errors in collection; GPS location and time of questionnaire administration will also be recorded to ensure that interviews are appropriately conducted and adequate time has been devoted to data collection.

Loss to follow-up will be minimized through the use of community health workers (CHWs) from each cluster to ensure children are available during monthly study visits. In the event of missing participants, the study team, assisted by CHWs, will undertake home visits to locate cohort members or may extend the monthly visits to each cluster to sample participants who are temporarily unavailable. Extended periods of time spent living away from a participant’s cluster will be recorded and factored into the analysis.

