Active monthly follow-ups will occur at village sentinel sites. CHWs will be responsible for organizing village leaders and parents in advance of the scheduled visit, including arranging for school-aged children to be monitored outside school hours. At each follow-up, the clinical team will administer a physical examination, as described above, and record a short medical history to assess recent febrile illness, LLIN use and health care-seeking behaviour. A blood specimen will be collected by finger-prick for an immediate mRDT; anaemia (moderate: haemoglobin 7–8 g/dl to severe: haemoglobin <7 g/dl) will be measured in children aged 6 to 59 months at enrollment, at 6 months and 1 year post-intervention. In the case of a positive mRDT, the child will receive a curative weight-appropriate course of ALU, unless the child is already taking an appropriate antimalarial or has been within the past 2 weeks.

During the course of the study, the clinical team will also provide treatment for non-malaria illnesses, including paracetamol if axillary temperature is ≥37.5 °C, amoxicillin for non-severe pneumonia, oral rehydration salts (ORS) plus zinc for gastroenteritis and ferrous sulphate plus albendazole for anaemia (haemoglobin <9 g/dl). Children with severe illness at any time will be referred to Teule district hospital for further management. Participants are also free to receive medication from health personnel outside of the study teams.

Enrolled cohort children will be provided separate study booklets that their parents or guardians will be instructed to present each time that their child visits a health facility during the follow-up period. The 24 health facilities serving the study area will be visited by the study teams prior to the start of the study. Healthcare workers will be trained to properly complete the study booklet for enrolled children, recording whether the child was tested for malaria either by microscopy or mRDT during the visit, the result of the test, and what medication was prescribed or administered. During the monthly follow-up visits, study teams will ask parents or guardians of enrolled cohort children to present the study booklets, and any data on interim health facility visits will be collected electronically. Parents and guardians will also be asked to describe any other illness episodes that were not recorded in the study booklet.

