### Study endpoints

#### Epidemiological

Primary endpoint: the cumulative incidence of malaria parasitaemia (asymptomatic and symptomatic) defined as the number of mRDT-confirmed episodes of parasitaemia per child per year. A child will be considered to have experienced an episode of parasitaemia during a given month if they had a positive mRDT during the scheduled monthly follow-up visit, irrespective of symptoms. Two consecutive positive scheduled mRDT results will be treated as two separate episodes and any malaria cases diagnosed and treated at health facilities between monthly visits will also be counted as episodes.

Secondary endpoints: (i) time to first episode of malaria parasitaemia (asymptomatic and symptomatic) as determined by mRDT as per the primary case definition; (ii) changes in mean levels of haemoglobin among cohort children aged 6 to 59 months.

All study outcomes will be compared between the intervention (ITWL + LLINs) and the control arm (LLINs only).

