### Sample size rationale

#### Epidemiological

LLINs can reduce malaria morbidity by approximately 40–70 % [3]; the impact of ITWL alone or in combination with LLINs on malaria is unknown. The effects may be additive or synergistic (e.g. by having a mass killing effect and/or reducing mosquito longevity) or antagonistic (e.g. if the LLINs are repellent thereby reducing mosquito house entry and contact with ITWL). Due to the intensity and projected cost of the ITWL intervention, a minimum reduction in malaria of 30 % is considered of public health importance.

For the cohort study, sample size is based on annual cumulative incidence of malaria infection in each study arm as the primary outcome. From baseline surveys conducted in Muheza, it was assumed that cumulative incidence of malaria would be 2.5–3.0 detected episodes/year, with a coefficient of variation (CV) between clusters of 0.302 and an intra-cluster correlation (ICC) of 0.047. Therefore with 22 clusters per arm, sampling an average of 110 children (assuming 18 % loss to follow-up) per cluster, the study will have >85 % power to detect a 30 % reduction in malaria incidence at the 5 % significance level [59].

To measure time to first malaria episode during the evaluation year, assuming an ICC of 0.047, for a cumulative incidence of 2.0 episodes/year, the monthly risk would be 0.167. Using a binomial distribution calculation, the probability of having zero positive determinations (i.e. of ‘surviving’ malaria-free) over 1 year is (1–0.167)^12^ = 0.112; with a monthly 30 % reduction in risk, the cumulative probability of having no monthly positive RDTs in 12 months in the intervention arm would be (1–0.117)^12^ = 0.226. Sampling from 44 clusters with 90 children per cluster, the study will have 99 % power to reject the null hypothesis of no difference in ‘survival’.

To assess the effectiveness of the interventions on anaemia in children aged 6 to 59 months, assuming mean haemoglobin of 10.75 g/dl, 22 clusters in each study arm and a CV of 0.048, the study will be able to detect a difference of 0.5 g/dl in mean haemoglobin with 5 % significance and 85 % power between the study arms, sampling an average of 45 children per cluster.

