### Data analysis

All statistical analyses will be performed using STATA version 13 (StataCorp LP, College Station, TX, USA). The primary endpoint will be a comparison of the cumulative incidence of symptomatic or asymptomatic episodes of malaria in children between the two intervention groups. Data from cohort members who are lost to follow-up or who missed monthly visit(s) will be treated as censored. Similarly, children who are taking anti-malarial drugs, based on a positive mRDT, will be excluded in the analysis for the first 2 weeks following treatment. History of travel away from the study village will be recorded during monthly visits and time at risk will be censored for such periods. In addition, malaria cases in children who resided outside their cluster area for more than half of the elapsed study period at the time of illness will be excluded.

An initial analysis will compare the cumulative malaria incidence rates between the two study arms to assess the number of episodes of malaria parasitaemia (symptomatic, asymptomatic or combined) per child per year. A follow-up analysis will examine the time to first episode of clinical malaria. The rate ratio (RR) will be calculated by dividing the incidence rate in the intervention relative to the control arm. The effectiveness of ITWL + LLINs vs. LLINs alone will be obtained from the final analysis as 1-RR. Cox regression modeling will be used to investigate potential confounding such as season and age. A priori confounders will be included in the model and that the presence of effect modification or interaction terms will be explored. Both intention to treat (all persons randomized) and per protocol analyses (all persons who received the intervention) will be conducted. All analyses will be adjusted for within-cluster correlation using generalized estimating equations or random effects models with gamma frailty. In addition, missing data will be analyzed and multiple imputation used, if required.

Similarly, mean haemoglobin in 6–59 month olds will be measured and compared between the two arms.

Other outcome variables, including entomological indices, cost-effectiveness and acceptability of interventions will be compared between study arms accounting for any correlated observations within clusters or households.

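### The haemoglobin endpoint is defined as a change but analysed and powered as a mean, with no stated role for the enrolment value and no loss allowance on its 45 children per cluster

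*Protocol article*

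**What the plan says.** All references are to the protocol article.

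- **Objective** (Secondary objectives, Epidemiological): the effect on mean haemoglobin concentration at 6 to 59 months.
- **Endpoint** (Study endpoints, Epidemiological): "changes in mean levels of haemoglobin among cohort children aged 6 to 59 months".
- **Analysis** (Data analysis): "mean haemoglobin in 6–59 month olds will be measured and compared between the two arms". The sentence opens with a word linking it to the paragraph before, which contains "A priori confounders will be included in the model" (written about Cox regression) and "All analyses will be adjusted for within-cluster correlation using generalized estimating equations or random effects models with gamma frailty".
- **Measurement** (Clinical evaluations and patient treatment): anaemia "will be measured in children aged 6 to 59 months at enrollment, at 6 months and 1 year post-intervention".
- **Stated use of baseline** (Randomization and blinding): baseline prevalence and haemoglobin "will be used to assess disparity in disease burden at the village level prior to study monitoring". No use in the comparison of arms is given.
- **Power** (Sample size rationale, Epidemiological): a 0.5 g/dl difference in means with 85 % power at the 5 % level, "assuming mean haemoglobin of 10.75 g/dl, 22 clusters in each study arm and a CV of 0.048", "sampling an average of 45 children per cluster". The primary calculation in the same section states 110 children with 18 % loss, and the time-to-first-episode calculation uses 90. The haemoglobin calculation mentions no loss.

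**The concern.** A change from enrolment, a follow-up mean and a follow-up mean adjusted for enrolment are three different analyses of the same data. They differ in precision and, when arms differ by chance at baseline, in their estimates. The article names the first as the endpoint, describes the second as the analysis, and does not mention the third. It also says that, with few randomised units, the arms cannot be assumed comparable on every factor and that baseline disparity will be examined. It does not say what follows if disparity is found, so the role of baseline could be settled after the imbalance is seen.

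The sample-size question is smaller. If 45 is an enrolled count, fewer children are analysed at follow-up. The article also leaves open whether a child who passes 59 months during the year is measured again. That affects data collection, and missing readings cannot be recovered at analysis.

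**Working it through.** **1. Reproducing the stated 85 %.** From the article: mean 10.75 g/dl, difference d = 0.5, CV k = 0.048, c = 22 clusters per arm, m = 45. Assumed: a two-sided 5 % test and a child-level SD s, which the article does not give. The cluster formula for means is

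V = 2s²/m + k²(μ₀² + μ₁²); power = Φ(√[(c − 1)d²/V] − 1.96).

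With s = 1.3 and means 10.75 and 10.25:

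- k²(μ₀² + μ₁²) = 0.002304 × 220.625 = 0.508
- 2s²/m = 3.38/45 = 0.075, so V = 0.583
- √(21 × 0.25/0.583) = 3.00; Φ(1.04) = 85.1 %

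With means 10.75 and 11.25, s = 0.78 gives 85.0 %. The stated figure therefore reproduces, but at an SD chosen to match it.

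**2. Children available per cluster.** The article gives no age distribution, so even ages are assumed. The 6–59 month band spans 54 months. The eligible range is 138 months if eligibility runs to the 12th birthday, or 126 if it stops at the 11th.

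| Stage | Calculation | Children |
|---|---|---|
| Enrolment | 110 × 54/138 to 110 × 54/126 | 43 to 47 |
| After 18 % loss | 90.2 × 54/138 to 90.2 × 54/126 | 35 to 39 |
| 18 % loss applied to 45 | 45 × 0.82 | 37 |
| 12 months, if those past 59 months are dropped | 90.2 × 42/138 to 90.2 × 42/126 | 27 to 30 |

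So 45 matches enrolment. To analyse 45 after loss would need 45/0.82 = 55 enrolled, half of the 110.

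**3. Power at those numbers** (same formula, s = 1.3).

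| m | 10.75 vs 10.25 | 10.75 vs 11.25 |
|---|---|---|
| 45 | 85.1 % | 82.1 % |
| 37 | 84.1 % | 81.2 % |
| 35 | 83.8 % | 80.9 % |
| 27 | 82.1 % | 79.2 % |

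The loss is about 1 point at 37 and about 3 points at 27. With s = 0.78 and 10.75 vs 11.25 it is smaller: 85.0, 84.6, 84.5 and 83.9 %. Numbers matter little because between-cluster variation dominates. At m = 37 it is 0.508 of V = 0.508 + 3.38/37 = 0.600, about 85 %.

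**4. Precision of the three analyses.** Let ρ be the baseline-to-follow-up correlation, taken as equal at child and cluster level, with equal variances at the two times. Relative to a comparison of follow-up means, the variance is 2(1 − ρ) for a change score and 1 − ρ² after baseline adjustment. The first is below 1 only when ρ exceeds 0.5. Since 1 − ρ² = (1 − ρ)(1 + ρ), the second never exceeds 1 or 2(1 − ρ).

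| ρ (assumed) | SE of change / SE of follow-up means | SE of adjusted / SE of follow-up means |
|---|---|---|
| 0.3 | 1.18 | 0.95 |
| 0.4 | 1.10 | 0.92 |
| 0.5 | 1.00 | 0.87 |
| 0.6 | 0.89 | 0.80 |
| 0.7 | 0.77 | 0.71 |

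**The case against.** The strongest reply is that this is a journal article, and the covariate list for a secondary outcome belongs in the full protocol or analysis plan. That holds for a list that is simply absent. It does not cover an endpoint named as a change in one section and as a mean in three others: those statements conflict, and the article does not settle which governs.

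Four stronger readings are tempting, and the documents do not support them.

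- **That the plan fixes an unadjusted comparison.** The haemoglobin sentence does not say so. Clustering adjustment is stated for all analyses, and nothing excludes a baseline term.
- **That the cohort cannot supply 45 children per cluster.** It can at enrolment. The shortfall concerns follow-up only, and the text does not say which stage 45 refers to.
- **That ageing-out breaks the pairing with baseline.** Entry starts at 6 months and participants are not replaced during surveillance. Any cohort child still under 60 months at 12 months was therefore due an enrolment reading. Numbers would fall, but the remaining pairs stay intact. The Design section, which describes surveying this cohort at all three times, can also be read as fixing the group at enrolment.
- **That baseline adjustment would bring a known, large gain in power.** No correlation is given. Curative treatment of every child at enrolment and new nets for all households could weaken the link between enrolment and 12-month values. This limits any claimed gain, but it is also the situation in which a change score does worst.

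It is also fair that 0.048 may be the CV of observed cluster means. With no separate child-level term, power is then 86.6 % (10.75 vs 11.25) or 89.5 % (10.75 vs 10.25), and step 3 would count child-level variation twice.

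**Conclusion.** The point holds in a limited form. The article does not reconcile a change in mean haemoglobin with a between-arm comparison of means, and it gives the enrolment value no role beyond describing disparity. Adjusting for that value is at least as precise as either stated form, apart from the small cost of estimating the coefficient. That ordering assumes equal variances at the two times; the size of the gain depends on a correlation the article does not give.

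The sample-size part is minor. The 45 carries no loss allowance, unlike the other two calculations in its section. About 37 (35 to 39) are expected at follow-up, costing about 1 point of power, or about 3 points at 27 children if those past 59 months are dropped. These figures rest on even ages and a child-level SD of 1.3 g/dl, both assumed. A reader might infer that the haemoglobin comparison is seriously underpowered; the arithmetic does not show that.

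**What to change.** 1. Use one definition in the objective, endpoint and analysis: haemoglobin at 12 months (and at 6 months), compared between arms by GEE or a linear mixed model. Include arm, enrolment haemoglobin (child value, cluster mean or both) and the prevalence stratum used in randomisation. Keep the clustering adjustment already stated.
2. State that the 6–59 month group is defined by age at enrolment, and that those children are measured again at 6 and 12 months even after passing 59 months.
3. Say whether 45 is enrolled or analysed. Restate the power with about 37 analysed children per cluster, and give the child-level SD and the meaning of the CV.

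The cost is a few lines of text, a stated power about 1 point lower, and some extra haemoglobin readings from finger-pricks already taken at the monthly visits.

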#### Household acceptability

To identify social, cultural and other factors that may affect acceptability of ITWL compared to LLINs in the study area.To assess perceptions regarding the implementation of ITWL among household members, community leaders, health workers and ITWL installers.

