### Social acceptability and economic evaluations

To identify social, cultural and other factors that may affect acceptability and uptake of ITWL and LLINs in the study area, a series of FGDs and IDIs will be undertaken. Four FGDs will be conducted in two randomly selected villages from each study arm prior to intervention and in the same villages after ITWL installation and LLIN distribution (total of 16 FGDs). FGDs will be conducted with small groups (8–12 participants) of men and women separately to reflect the different roles played in Tanzanian society and to ensure that all members will feel able to contribute to the discussion. In each village, one FGD will comprise heads of households and the other mothers of children <5 and mothers of children aged 5 to 11 years old. FGDs will be led by a trained moderator who will use a guide with open-ended questions to explore with the group a series of broad topics relating to malaria, disease prevention, ITWL concept and installation, LLIN use and healthcare seeking behavior and access. FGDs will be digitally recorded with consent from participants and a note-taker will document all non-verbal communications.

IDIs will be conducted with village or hamlet leaders, CHWs from village health facilities and ITWL installers to explore the opinions of key individuals who may play important roles in influencing community members’ perceptions of ITWL and LLIN use. Four IDIs will be conducted per study arm prior to intervention and with the same individuals after ITWL installation and LLIN distribution (total of 16 IDIs). The IDIs will cover a range of similar topics to the FGDs. IDIs will be conducted by a trained interviewer and digitally recorded with participant’s consent; non-verbal communication will be documented by hand. Informal community observations relating to major study activities, including community sensitization meetings, ITWL installation and LLIN distribution, will also be recorded by the study teams. Following the FGDs and IDIs, the main themes identified will be used to design a standardized, closed-ended quantitative acceptability questionnaire to be administered at three, six and 12 months post-intervention.

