Digitally recorded FGDs and IDIs will be transcribed and translated verbatim and the data analysis procedure will follow a bottom-up approach by coding the raw data line-byline. The coding will be done by two research assistants to ensure intercoder reliability. Themes and theoretical constructs will emerge and will be grouped together as per the objectives. This method reflects a more analytical approach and will borrow the iterative approach of grounded theory analysis [60]. Data will be organized by importing into new QSR Nvivo 10 workbook and filed into the ‘internals’ section. Transcripts will be coded in an ongoing process as data is collected whereby a coding template will be developed from initial transcripts. As more data is received and coded, the template will be further refined to reflect any new emerging ideas or themes. These will appear in Nvivo as nodes which will be arranged in groups under a parent node labeled with the theme. Beyond this, themes may be organized into wider groups representing theoretical constructs. Memos will be made to explain the justification behind forming the construct. The social scientists from the project together with the wider research team will develop a narrative linking the original research objectives with the participants’ subjective practices and experiences. The aim of these theoretical descriptions will be to reiterate the participants’ narratives in terms of the theoretical constructs.

Quantitative data derived from household acceptability questionnaires will be compared using appropriate summary statistics, such as mean differences and proportions. All exposure variables showing evidence of relationships with acceptability of the study intervention in univariate analysis will be fitted in a multivariable logistic regression model. A stepwise backwards strategy will be used to eliminate variables with no effect (p > 0.05), these multilevel models will adjust for clustering within village or household and investigate for possible confounding or interaction.

Economic data collected will be used to assess the direct and indirect costs per malaria episode averted in each study arm.

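### Acceptability factors are chosen by univariate screening and backward elimination at p > 0.05, which risks exaggerated estimates and poorly covering intervals for the factors kept and treats non-significance as absence of effect

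*Protocol article*

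**What the plan says.** The Data analysis section of the protocol article sets two selection steps for the quantitative acceptability data.

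- Screening: "All exposure variables showing evidence of relationships with acceptability of the study intervention in univariate analysis will be fitted in a multivariable logistic regression model". No screening threshold is given.
- Elimination: "A stepwise backwards strategy will be used to eliminate variables with no effect", with p > 0.05 as the criterion.

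The same sentence adds that "these multilevel models will adjust for clustering within village or household and investigate for possible confounding or interaction".

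The model serves a stated secondary objective under Household acceptability: "To identify social, cultural and other factors that may affect acceptability of ITWL compared to LLINs in the study area". On the source of the candidate variables, the section on social acceptability and economic evaluations says that "the main themes identified will be used to design a standardized, closed-ended quantitative acceptability questionnaire to be administered at three, six and 12 months post-intervention".

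For the malaria models the same Data analysis section takes a different line: "A priori confounders will be included in the model".

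**The concern.** Three things are wrong with the rule as written.

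1. It equates p > 0.05 with absence of effect. A non-significant result may only mean that the data were too few, so this is an error whatever the sample size.
2. A factor survives only if its estimate is large relative to its standard error in these data. Survivors are therefore a selected set: their estimates lean away from zero, and ordinary 95% intervals no longer have 95% coverage for that set. The section states no allowance for this.
3. A confounder matters through what it does to other estimates, not through its own p-value. The sentence promises to look at confounding, but no clause keeps a confounder with p > 0.05, and one that fails the univariate screen never enters.

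At stake is how far the list of factors said to affect acceptability of the wall lining, and the strength attached to each, can be believed.

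**Working it through.** **Inputs.** The only figure in the document is the removal threshold, p > 0.05. It gives no number of candidate factors, number of respondents, effect sizes or screening threshold, and no power or error rate for this model, so there is no figure to reproduce. Everything below rests on assumed ranges, in ordinary logistic regression without clustering.

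**1. Chance findings: does the rule create them?** With k independent unrelated factors each tested once at 0.05 and no selection, the chance of at least one false factor is 1 − 0.95^k:
- k = 10: 1 − 0.95^10 = 40.1%, expected number 0.5
- k = 20: 1 − 0.95^20 = 64.2%, expected number 1.0

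Simulating the two-step rule with 440 respondents, all factors unrelated and a screen at p < 0.2 gives about 42% and 62%, which is the same thing. In simulations that also contain real factors (n = 440), the mean number of false factors, stepwise against full model, is about 0.26 v 0.26 over 5 pure-noise factors and 0.78 v 0.82 over 15. This is multiplicity, and a full model does not reduce it.

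**2. Coverage of what is reported.** With 20 candidates, n = 200 to 1500 and log odds ratios of 0.1 to 0.4 per SD:
- stepwise, retained factors: about 50-84% of nominal 95% intervals cover the truth, and real factors are dropped in about 7-77% of cases
- full prespecified model, all factors: 94-95%

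Simple arithmetic shows where this comes from. A pure-noise factor kept at p < 0.05 has an interval that excludes its true value, zero, by construction. Take 5 real and 15 noise factors, about 0.78 noise factors kept, and 95% coverage for the real ones kept:
- 77% of real factors dropped: 5 × 0.23 = 1.15 kept; coverage (1.15 × 0.95)/(1.15 + 0.78) = 57%
- 7% dropped: 5 × 0.93 = 4.65 kept; coverage (4.65 × 0.95)/(4.65 + 0.78) = 81%

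So most of the shortfall comes from reporting only survivors. The rest comes from exaggeration of weak real factors in small samples.

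I repeated the simulation as a check: 5 real and 15 noise factors, independent normal variables, screen at p < 0.2, baseline log odds 0.8, n = 200, 440 and 1500, log odds ratios all 0.2, all 0.4 or mixed 0.1 to 0.4, 250 data sets each. Coverage was 52-86% for retained factors and 94-96% for all factors in the full model. Retained real factors with log odds ratio 0.2 were overestimated about 2.1-fold at n = 200 and hardly at all (1.06-fold) at n = 1500. If only the significant rows of the full model are read, coverage falls to 49-84%, much as under the stepwise rule.

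**3. Loss of a confounder.** One real confounder, correlated 0.5 with a null exposure, 10 or 20 candidates, screen at 0.05 or 0.20, 300 data sets per setting. Chance that the confounder is dropped:

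| log OR per SD | n = 200 | n = 500 | n = 1500 |
|---|---|---|---|
| 0.2 | 77-82% | 45-52% | 6-10% |
| 0.4 | 32-34% | 2-4% | 0% |

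In these runs the null exposure itself was kept in 1-9% of data sets, so the damage to that neighbouring estimate was limited.

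**The case against.** The strongest case against is that this is method preference in an exploratory secondary analysis. The questionnaire is built from focus-group and interview themes, so much of the candidate pool is bounded before any quantitative data exist. The section commits to multilevel adjustment and to examining confounding, and a condensed article may leave a rule for retaining confounders to the full protocol. It discloses the selection and does not say that survivors will be presented as a model fixed in advance. Acceptability factors are also studied qualitatively.

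Much of this stands, and it rules out several stronger readings.

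- A reader might infer that the rule manufactures false factors, citing some 40% or 60% of data sets with at least one. Those are the ordinary multiplicity figures and apply equally to the remedy if its p-values are read at 0.05.
- A reader might infer that real confounders will be lost. That ranges from about 82% of data sets to none, depending on inputs the document does not give. It is a risk, not a certainty.
- A reader might infer that the list would decide roll-out. The Discussion names levels of acceptability as one element of operational success and ties scale-up to relative cost-effectiveness; it does not say that this factor list would guide it.

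What does not fall is the rule itself. It is stated, not merely left open, and it calls non-significant variables ineffective. Naming themes beforehand does not help if the data then decide which are reported. The malaria models in the same section show that the plan accepts a priori confounders elsewhere.

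**Conclusion.** The point holds as a minor one. Screening and eliminating by p-value, then estimating on the same data, risks exaggerated estimates and unreliable intervals for the retained acceptability factors, and can discard real factors or confounders; reading p > 0.05 as no effect is wrong in itself.

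The size, about 50-84% coverage for retained factors against 94-95% over all factors in a full model, is illustrative. It assumes 20 candidates, 200 to 1500 respondents, log odds ratios of 0.1 to 0.4 per SD and no clustering, none of which the document supplies. The advantage of the full model depends on reporting every estimate.

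The scope is narrow. The malaria endpoints do not use this rule, and the between-arm comparison of acceptability is described separately. No trial effect estimate changes.

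**What to change.** Replace the screening and elimination wording with the following.

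- Name the candidate factors, from the focus-group and interview themes, and the known confounders before the questionnaire data are opened.
- Fit one multilevel logistic model containing all of them, and keep each whatever its p-value.
- If there are too many for the number of less common responses, use penalised estimation (ridge or Firth) rather than deletion.
- Report every estimate with its interval, not only the significant ones, and label the analysis exploratory.
- Delete the phrase that equates p > 0.05 with no effect.

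The cost is a few sentences of analysis text, a less parsimonious model and somewhat wider intervals. The change does not reduce the expected number of chance findings. The exploratory label and full reporting are what let a reader allow for them.
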